### Recruitment

Potential study participants will be identified from a list provided by each PHC center. Two research assistants (Rs), both clinical psychologists, will be in charge of calling the mothers included in the list, verify by telephone whether they meet the inclusion criteria, and explain the study in detail. Mothers who meet the inclusion criteria and are interested in participating will be sent an online protocol that will include informed consent. Mothers who do not wish to participate will be asked for the reasons. Once the mother provides electronic consent, the initial evaluation scales (EPDS, ASQ:SE- 2, MPAS, and CEQ) and a sociodemographic survey will be sent to her electronically. Finally, the mother and RA will agree upon at a time to make a video call to record 5 minutes of free play required by the ESA.

### Assignment of Interventions

#### Sequence Generation

To generate the random allocation sequence, we will use a computer software program called Studyrandomizer using permuted block randomization with a block size of 5 in a 3:2 ratio.

#### Concealment Mechanism

Allocation concealment will be ensured because the randomization code will not be released until all patients have been recruited and all initial measurements have been completed.

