### Participant Timeline

The study duration for the participants will be 3 months, regardless of study arm allocation. This study does not have a follow-up phase. The total trial data collection period will be approximately 14 months.

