#### Implementation

After each participant signs the informed consent and performs baseline measurements, the RA recruiting the participant will contact another investigator to request the arm to which the participant has been randomized (intervention or intervention plus TAU). Thus, the enrollment of the participants will be performed by a different RA from the one who will generate the randomization sequence. The investigator will not be aware of the results of the initial evaluation. After completing the initial evaluation, the RA, who is blind to the random allocation sequence, will notify the participants of the type of intervention to which they will be assigned.

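### Concealment is said to rest on withholding the code until recruitment ends, yet arms are released mother by mother to the recruiter from fixed blocks of 5, so some upcoming arms could be deduced

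*Protocol article*

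**What the plan says.** Under Concealment Mechanism, the protocol article says concealment is secured because "the randomization code will not be released until all patients have been recruited and all initial measurements have been completed".

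Implementation describes a different process, triggered by each mother's own consent and baseline rather than by the end of recruitment. At that point "the RA recruiting the participant will contact another investigator to request the arm to which the participant has been randomized". Then "the RA, who is blind to the random allocation sequence, will notify the participants of the type of intervention to which they will be assigned".

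Sequence Generation specifies "permuted block randomization with a block size of 5 in a 3:2 ratio". It mentions no variation in block size and no stratification.

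Recruitment names two RAs, who "will be in charge of calling the mothers included in the list, verify by telephone whether they meet the inclusion criteria". They also explain the study, and an RA arranges the baseline video call with the mother.

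On timing, the abstract and Results place enrolment from August 2021 to August 2022. Secondary Outcome Measures sets the second assessment 2 to 3 months after the first. Participant Timeline states: "The study duration for the participants will be 3 months, regardless of study arm allocation".

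**The concern.** Concealment means that whoever decides whether and when to enrol a mother cannot foresee her arm. The article attributes this to a safeguard that its next section does not apply. What Implementation does provide is useful: a separate person holds the list, and the arm is requested only after consent and baseline. That keeps a mother's own baseline independent of her released arm. It does not keep the next mother's arm hidden from a recruiter who has watched earlier arms come out of small blocks of constant size.

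The same RAs call, screen and invite mothers and schedule their baseline. Workshops need 3 to 6 dyads, so there is also a practical reason to time an enrolment. The exposed quantities are the between-arm differences in clinical outcomes, which Expected Findings says will be used to estimate the sample size of the later trial.

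**Working it through.** **Inputs.** Block of 5 with 3 intervention (I) and 2 control (C), from Sequence Generation. Total of 50, from Sample Size. Two RAs, from Recruitment. Enrolment of 12 months, from the abstract and Results. Second assessment at 2 to 3 months, from Secondary Outcome Measures.

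**The plan's own figure.** 2 × 25 = 50 mothers, which is 50/5 = 10 complete blocks, or 30 intervention and 20 control. The article gives no figure for predictability.

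**Step 1: can all arms be withheld?** A mother enrolled in August 2021 would learn her arm about 12 months later, but her second assessment is due at 2 to 3 months. Literal withholding is not workable, so the mother-by-mother release in Implementation is what will operate.

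**Step 2: full information.** Assume the recruiter knows the block size and every earlier arm. An allocation is certain once one arm's quota in the block is used up. Over the 10 equally likely orders of IIICC:

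| Position in block | 1 | 2 | 3 | 4 | 5 | Sum |
|---|---|---|---|---|---|---|
| P(arm certain) | 0 | 0 | 0.10 | 0.40 | 1.00 | 1.50 |
| P(best guess correct) | 0.60 | 0.60 | 0.70 | 0.70 | 1.00 | 3.60 |

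The closed form agrees: 3/(2+1) + 2/(3+1) = 1.0 + 0.5 = 1.5 per block. That is 1.5/5 = 30%, or 0.30 × 50 = 15 mothers. Best-guess accuracy is 3.60/5 = 72%, against 60% from always guessing intervention.

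**Step 3: two RAs, one list, no communication.** Assume each mother is equally likely to be handled by either RA, and that an RA sees only her own earlier allocations in the block. Certainty then requires that she handled both earlier controls (probability 1/4) or all three earlier interventions (1/8).

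- Position 3: 0.10 × 1/4 = 0.025
- Position 4: 0.30 × 1/4 + 0.10 × 1/8 = 0.0875
- Position 5: 0.60 × 1/4 + 0.40 × 1/8 = 0.200

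The sum is 0.3125 per block, and 0.3125/5 = 6.25%, about 3 of 50 mothers. A simulation gave 6.3%. This still lets each RA know where blocks begin.

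**Step 4: alternatives under full knowledge of past arms.**

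- Fixed blocks of 10 (6:4): 1.77/10 = 17.7% certain.
- Random mix of blocks of 5 and 10, order of sizes unknown (simulated, 50 mothers): about 6.6% certain, with best-guess accuracy about 69%.

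**The case against.** The strongest reply is that the randomization code means the complete list. On that reading Concealment Mechanism and Implementation do not conflict: the list stays closed while individual arms are issued from it. This is a fair reading, and a claim that the two sections contradict each other under every reading would go too far. It does not restore concealment, though, because a closed list hides nothing that can be deduced from the arms already issued.

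A reader might also infer that 30% of allocations will be predictable. The article does not support that as a fact. It describes the recruiting RA as blind to the sequence, never says that RAs were told the block size, and does not say whether the two RAs share allocations or have separate lists by center. Publication cannot have revealed the block size early on: the article cites an ethics renewal of January 6, 2022, about five months after enrolment began. So 30% is an upper bound.

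A reader might further infer that the recruitment rate, a primary outcome, is biased. Steering is possible in principle, but eligibility and recruitment rates are not comparisons between arms, and nothing in the article gives a size or direction for such a bias. Sample Size also says no hypotheses will be tested, and the clinical comparison is secondary. These points limit the severity. They do not remove the exposure of the between-arm estimates.

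**Conclusion.** The point holds in a limited form. The stated basis for concealment does not describe the procedure that will run, and that procedure leaves some later arms deducible. The size ranges from about 6% of allocations (two RAs on one list, not communicating) to 30%, or 15 of 50 (RAs who communicate, or who each see a complete list). Both figures assume that recruiters know the block size and can tell where blocks start; without that knowledge the risk is lower. No actual steering is shown or alleged. In a feasibility trial with these protections for the current mother's baseline, this should be fixed, but it does not invalidate the primary aims.

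**What to change.** 1. In Concealment Mechanism, delete the claim that the code is withheld until everyone is recruited. State instead that an independent list holder releases each arm one at a time, after that mother's consent and baseline.
2. For mothers still to be enrolled, regenerate the list with randomly varying blocks of 5 and 10, and do not disclose the sizes to recruiters. This brings certain allocations to about 6.6% even if all past arms are known. Best-guess accuracy falls only from 72% to about 69%, so the third change is also needed.
3. Have the list holder, not the recruiting RA, tell each mother her arm, so that recruiters do not routinely see past allocations.

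The cost is revised wording, a regenerated list and some contact time for the list holder. The final split may depart slightly from 30:20 if the last block is incomplete. For example, if a block of 10 started at mother 46 of a fully mixed list, 1 to 5 of the last five would be intervention, giving 27 + 1 = 28 to 27 + 5 = 32.

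Releasing arms in complete batches is less suitable. At an even 50/12 = 4.17 mothers per month, the first mother in a batch of 10 waits 9/4.17 ≈ 2.2 months. Adding 4 weeks of sessions (about 0.9 months) gives about 3.1 months, beyond the 2 to 3 month assessment window. A batch of 5 yields exactly 3 intervention mothers, which leaves no margin above the minimum workshop size.

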#### Implementation

After each participant signs the informed consent and performs baseline measurements, the RA recruiting the participant will contact another investigator to request the arm to which the participant has been randomized (intervention or intervention plus TAU). Thus, the enrollment of the participants will be performed by a different RA from the one who will generate the randomization sequence. The investigator will not be aware of the results of the initial evaluation. After completing the initial evaluation, the RA, who is blind to the random allocation sequence, will notify the participants of the type of intervention to which they will be assigned.

#### Blinding

Trial participants will be blinded to the conditions of the 2 arms; they will know the type of intervention to which they are assigned, but they will not know which of the interventions is considered the control. The intervention providers will be instructed not to disclose the treatment that participants are receiving. Follow-up measurements will be taken blindly for the assigned group. The assessments of outcome variables will be conducted by RAs who are blind to the treatment allocation.

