## Methods

### Trial Design

This is a data analyst–blind, superiority, pilot feasibility study with a mixed design. The quantitative component is a 2-arm randomized parallel group of 50 mothers of infants aged 6-12 months who receive health care in 2 PHC centers in Santiago, Chile. Mothers will be randomized into the intervention or control group in a to 3:2 ratio (with more people allocated to the intervention arm). Both groups will receive the usual treatment and educational brochures provided by the PHC center, with the intervention group also receiving the C@nnected videoconferencing intervention. The qualitative component will consist of semistructured interviews with intervention providers to identify possible improvements and core components of the intervention as well as focus groups with mothers participating in the intervention to evaluate user acceptability and satisfaction with the implementation.

This type of study is suggested by the literature as an initial requirement for the implementation of an innovative intervention before applying it on a larger scale. It is also recommended to use quantitative and qualitative methodologies to evaluate feasibility and acceptability [29]. This clinical trial protocol follows the SPIRIT (Standard Protocol Items: Recommendations for Interventional Trials) and [30] and CONSORT (Consolidated Standards of Reporting Trials) guidelines [31]. Figure 1 provides a flowchart of the study process.

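### Blind outcome assessment is claimed for all outcomes, but four of the five post-intervention instruments are completed by mothers who know their arm, and no step is given that keeps the filming RA blind

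*Protocol article*

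**What the plan says.** All references are to the protocol article.

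- **Blinding** covers outcomes without exception: "The assessments of outcome variables will be conducted by RAs who are blind to the treatment allocation". It says separately that follow-up is measured without knowledge of the group. On the mothers it says: "Trial participants will be blinded to the conditions of the 2 arms; they will know the type of intervention to which they are assigned". What is withheld from them is which arm counts as the control.
- **Abstract (Methods)** describes a single-masked study in which the outcome assessor is the masked party.
- **Trial Design** names someone else: "This is a data analyst–blind, superiority, pilot feasibility study with a mixed design".
- **Recruitment**: "Two research assistants (Rs), both clinical psychologists, will be in charge of calling the mothers included in the list".
- **Implementation**: after consent and baseline, "the RA recruiting the participant will contact another investigator to request the arm to which the participant has been randomized". The RA, described there as blind to the allocation sequence, then "will notify the participants of the type of intervention to which they will be assigned". Enrolment is also said to be "performed by a different RA from the one who will generate the randomization sequence".
- **Data Collection**: after the intervention both groups complete EPDS, ASQ:SE-2, MPAS and CEQ again. The new ESA video is recorded by an RA who must differ from the one who delivered the intervention. No other separation is stated there.
- **Changes in Maternal Sensitivity**: the ESA videos are scored by coders from outside the research team who do not know the arm.

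**The concern.** There are two problems, of unequal strength.

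The first is that the blinding claim does not match how the scores arise. On a self-completed questionnaire the respondent is the assessor, and here she knows whether she attended the workshop or received only brochures. No arrangement of RAs changes that. The Objective section makes the estimation of effect sizes on sensitivity, depressive symptoms, attachment and socioemotional development a secondary aim, and Secondary Outcome Measures says the clinical measures are to guide the sample size of the next study. If questionnaire effects are carried forward as blind-assessed, their exposure to expectation, which would probably favour the workshop, is hidden from whoever plans that trial.

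The second is that blind follow-up has no described route. Being blind to the sequence protects allocation concealment before assignment. It does not make an RA blind to an arm that the RA has just requested and announced. An RA who knows the arm and then runs the follow-up play session could affect what is filmed, even though the later coding is blind.

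**Working it through.** No sample size, power or error-rate figure bears on this point, and the plan gives no figure to reproduce. The check is a count of instruments by who produces the score, followed by a reading of the staff roles.

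**Step 1: who produces each score after the intervention**

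| Instrument | Source section | Who produces the score | Knows the arm? |
|---|---|---|---|
| CEQ | Acceptability (Quantitative Assessment) | Mother; described as self-report | Yes |
| EPDS | Changes in Maternal Depressive Symptoms | Mother; described as self-administered | Yes |
| MPAS | Changes in Postpartum Maternal Bonding | Mother; described as self-report | Yes |
| ASQ:SE-2 | Recruitment; Data Collection | Mother; sent to her at baseline and completed again afterwards | Yes |
| ESA | Changes in Maternal Sensitivity | External coders | No |

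The ASQ:SE-2 is not labelled self-report in the article. Its place in the table rests on how it is sent out and completed. That mothers know their arm rests on Blinding: "they will know the type of intervention to which they are assigned".

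**Step 2: counts**

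- All instruments: 4 of 5 = 80% are scored by a person who knows the arm.
- Clinical scales only (ESA, EPDS, ASQ:SE-2, MPAS): 3 of 4 = 75%.
- Instruments whose score is described as produced by an RA: 0 of 5.

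Read literally, the sentence about blind RAs describes the scoring of none of the five instruments. The only post-intervention RA task the article describes for these instruments is recording the video.

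**Step 3: masked parties named**

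- Abstract: outcome assessor, single-masked.
- Trial Design: data analyst.
- Blinding: participants and outcome assessors.

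A single-masked study cannot have all of these as its one masked party.

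**Step 4: RA roles and what each knows**

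- Recruiting RA: requests the arm mother by mother, so knows it for each mother recruited.
- Sequence-generating RA: a different person from the enrolling RA; has generated the allocation sequence.
- RA who provided the intervention (Data Collection's wording allows for one): knows the arm of the mothers in the workshop.
- RA filming at follow-up: must differ from the provider (Data Collection) and must be blind (Blinding). No section says this RA must differ from the one who learned that mother's arm.

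The requirement of blindness is therefore written down, while the only separation written down leaves the recruiting RA eligible to film.

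**The case against.** The strongest reply concerns the RAs. Recruitment assigns two RAs to calling mothers; it does not say the study has only two. Implementation refers to a further RA role, and Blinding already requires blind follow-up. Separate staff, or two RAs filming each other's recruits, would satisfy it. This stands. A reader might infer that the recruiting RA films the same mothers at follow-up, or try to estimate what share of the videos is affected. The documents support neither: no section says who films beyond the rules above, and nothing gives a division of the work.

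The second reply is that the mothers' knowledge is disclosed. The sentence calling them blinded states its own limit, the abstract claims masking of the assessor only, and three of the questionnaires are openly described as self-completed. That softens any suggestion of concealment. It does not rescue the sentence that covers outcome variables without exception. Not being told which arm is the control is also thin protection: the RAs explain the study in detail, and control mothers receive brochures summarising workshop sessions they do not attend.

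The third reply is that little depends on it. Eligibility, recruitment, adherence and follow-up proportions do not need blind rating. CEQ asks about credibility and satisfaction, so the respondent has to know what she received. No hypotheses are to be tested. ESA, the intended main outcome of the later trial, is coded blind from free play with one fixed instruction. All of this is fair and limits the severity. What remains is the use of three self-reported clinical scales to inform the next trial under a description that does not apply to them.

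**Conclusion.** The point holds in two parts.

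The masking statement is wrong for four of the five post-intervention instruments (three of the four clinical scales, plus CEQ), and the article names the masked parties inconsistently in three places. This needs no assumption beyond treating the ASQ:SE-2 as completed by the mother, which is how the article describes its use.

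The blind follow-up promised in Blinding has no stated mechanism, because the recruiting RA learns the arm and the filming RA is separated only from the provider. This is a gap in the procedure, not evidence that any follow-up video was or will be made by an unblinded RA. No proportion can be attached to it.

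ESA scoring is adequately protected; only the filming is exposed. The consequence falls mainly on how the questionnaire effects are described and reused. The changes should be made, but the point does not threaten the feasibility aims.

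**What to change.** 1. **Notification.** In Implementation, have the investigator who holds the allocation list tell the mother her arm, so that the recruiting RA never learns it. Alternatively, leave notification as it is and state in Data Collection that the follow-up video is recorded by an RA who has not learned that mother's arm.
2. **One masking statement**, used in the Abstract, Trial Design and Blinding: the ESA coders and the RA recording the follow-up video are blind; participants are not, and therefore EPDS, MPAS, ASQ:SE-2 and CEQ are not blind-assessed. If the data analyst is also to be blind, say so in the same statement.
3. **Reporting and reuse.** State that effect estimates on those four instruments are reported as unblinded self-report and enter the planning of the next trial as such.

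Cost: at most one telephone call moves to a person already in the procedure, and a few sentences change. No extra staff or participants are needed. Relabelling does not remove expectation bias from the questionnaires; it stops them being read as blind-assessed.

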#### Harms

No harm or risk to participants from this study is expected to occur. In cases where any alteration is detected in the postpartum depression and socioemotional development assessment scales, the mother will be informed and, with her consent, referred for management at her PHC center.

### Data Collection

Data obtained from the sociodemographic survey and the quantitative evaluations will be stored electronically and will not be linked to the identities of the participants. The data will be in a different spreadsheet than the one with personal data, which only 1 RA has access to, thus ensuring that the identity of the participants is protected.

Once the intervention is complete, both groups will complete the scales again (EPDS, ASQ:SE- 2, MPAS, and CEQ), and a new video recording (ESA) will be made by an RA different from the one who provided the intervention. Finally, the qualitative evaluation of the process will be carried out.

Data obtained from the qualitative information (the interviews and focus groups) will be recorded, transcribed, and assigned codes that will ensure the anonymization and protection of the participants’ identities.

### Data Analysis

For the quantitative analysis, descriptive statistics will be used for the clinical and sociodemographic variables of the groups, eligibility rate, recruitment, and adherence. Analysis of covariance (ANCOVA) will be used to determine differences in clinical outcomes between the groups. Data analysis will be conducted using SPSS Statistics 27 software (IBM Corp).

For the qualitative analysis, interviews and focus groups will be analyzed considering the conceptual basis of the Framework Analysis Approach [46], which is commonly used for thematic analysis of semistructured interview transcripts. It allows for the identification of commonalities and differences in qualitative data to draw descriptive and explanatory conclusions grouped around themes. It is different from Grounded Theory, which involves making systematic comparisons between cases to refine each topic and is aimed at generating social theory [47]. The Framework Analysis Approach is best suited to research that has specific questions, a limited time frame, a predesigned sample (eg, mothers and professionals participating in the intervention), and a priori issues (eg, evaluation of implementation of an intervention)

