### Objective

The primary aim of this paper is to report on the protocol comprising a pilot randomized feasibility trial to evaluate the feasibility and acceptability of C@nnected, a group videoconferencing intervention that aims to improve maternal sensitivity in mother-infant dyads attending PHC centers in Chile. Along with detailing the intervention, this paper provides an account of the plan to collect both quantitative and qualitative measurements of outcomes.

The secondary aims are to (1) to estimate the effect size in clinical outcomes between the groups after the intervention in terms of maternal sensitivity, postpartum depressive symptoms, postpartum attachment, and socioemotional development; and (2) identify the key parameters for the implementation and evaluation of the intervention, which will enable the design of an effectiveness study in the future.

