### Interventions

#### Control Arm (Treatment as Usual Plus Educational Brochures)

Participants of this study are patients of the Chilean public health system and are supported by the Chile Crece Contigo national comprehensive child protection system. Some of the benefits are health checks during pregnancy, care during labor and delivery, child health checks, delivery of material for early stimulation, and detection and timely treatment of developmental delays [26].

In addition to receiving treatment as usual (TAU) at their PHC center, the control group will receive digital brochures with information on early parenting (once a week for 4 weeks). These brochures will summarize the content of each workshop session and the homework to be complete as a family. These are the same brochures handed out after each session in the intervention group.

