The intervention is aimed at mother-infant dyads and consists of 4 sessions delivered over the course of 4 weeks, at 2 hours per week. Each group will include a minimum of 3 and a maximum of 6 dyads per group led by a trained provider. The activities are protocolized in a manual and are designed to be carried out with the infant. The manual specifies the structure and content of each session, the details of the materials to be used, relevant aspects to be emphasized during the activities, and additional information that delves more deeply into the issues addressed in the workshop. This aims to ensure the comprehensive replication of the intervention, which has been associated with the best effectiveness in this type of intervention [34]. Table 1 shows the main components of the intervention.

The adaptation to the video conferencing format was carried out between May and July 2021 by 2 authors of the face-to-face intervention in conjunction with a designer experienced with digital interventions. We used the recommendations of the Early Intervention Foundation [21] to achieve good results in virtual interventions as a frame of reference, which include the use of engagement elements and mechanisms to improve adherence and flexibility.

We reviewed the complete content of the workshop, adjusted the sessions to 1.5 hours, and adapted the training manual and all the activities for use in a web-based group environment. We aim to provide lighthearted and interactive activities to allow all participants to understand and share their experiences. In addition, we have included some activities associated with the impact of the COVID- 19 pandemic. Figure 2 is a screenshot showing an example of a videoconference session, and Figure 3 shows 4 examples of activities that will take place in the workshop.

**Table 1 table1:** Main components of the intervention with the objectives and activities of each session outlined.

Session	Name	Objectives	Examples of activities
1	“Knowing each other around attachment”	Achieve group cohesion Provide knowledge about attachment Recognize expected affective behaviors in an infant	Dynamics of presentation Difficulties in motherhood Common myths on attachment and parenting

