### Sample Size

As this is a feasibility study, no hypotheses will be tested, and a formal power calculation is not required [44,45]. However, the evidence suggests a sample size of 25 people per arm for a small effect size of 0.2, which is suitable for clinical feasibility trials [45]. Therefore, a sample size of 50 participants was established, and the 3:2 allocation was chosen considering possible partial adherence to the intervention.

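### The clinical comparison uses ANCOVA although only the intervention arm is treated in workshops of 3 to 6; if the workshop ICC is positive, the precision of the effect size for the next trial is overstated

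*Protocol article*

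**What the plan says.** - **Design.** Trial Design: "The quantitative component is a 2-arm randomized parallel group of 50 mothers of infants aged 6-12 months". Mothers are randomised individually, "using permuted block randomization with a block size of 5 in a 3:2 ratio" (Sequence Generation).
- **Intervention arm.** Delivery is in groups: "Each group will include a minimum of 3 and a maximum of 6 dyads per group led by a trained provider". Each workshop runs for four weekly sessions. The mothers agree a common time and have a telephone chat group, and group cohesion is a listed objective of session 1 (Table 1).
- **Control arm.** Usual care plus weekly digital brochures for four weeks, with no group contact.
- **Analysis.** The between-arm comparison has one sentence: "Analysis of covariance (ANCOVA) will be used to determine differences in clinical outcomes between the groups". The section mentions neither workshop nor provider, and the article lists no ICC among its outcomes or parameters.
- **Use of the results.** Secondary aim 1 is to estimate clinical effect sizes. Secondary aim 2 is to "identify the key parameters for the implementation and evaluation of the intervention, which will enable the design of an effectiveness study in the future". Secondary Outcome Measures and Expected Findings both say that the clinical results will guide the sample size of the later trial. The section on maternal sensitivity names that outcome as the later trial's primary outcome.
- **Inference.** Sample Size: "no hypotheses will be tested, and a formal power calculation is not required".

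**The concern.** Individual randomisation does not make outcomes independent when treatment is then given in groups. Mothers in one workshop share a provider, other participants, activities and a chat group, so their outcomes may resemble each other more than those of mothers in different workshops. This can happen in the intervention arm only, which makes the design partially nested. ANCOVA has a single independent residual per mother and leaves out the between-workshop variance.

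Two things are at stake, both in planning. The uncertainty reported around the effect size would be too small for any positive workshop ICC. The analysis would also give no estimate of workshop clustering, which bears directly on the sample size of a later trial of the same group-delivered intervention.

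**Working it through.** **Plan's own figure.** The stated size is a cited rule of thumb, "the evidence suggests a sample size of 25 people per arm for a small effect size of 0.2", giving 50 in total. It is not a power calculation, so there is no formula to reproduce. The split is 50 × 3/5 = 30 intervention and 50 × 2/5 = 20 control.

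**Inputs from the article.** 30 and 20 mothers; workshop size m from 3 to 6, hence 30/6 = 5 to 30/3 = 10 workshops; no clustering in the control arm.

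**Assumed inputs.** Workshop ICC of the baseline-adjusted outcome, 0.01 to 0.20 (not given in the article); equal total variance in the two arms; equal workshop sizes.

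**Step 1: design effect, intervention arm only.** DE = 1 + (m − 1) × ICC.

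**Step 2: true SE relative to the independence SE.** Ratio = √[(DE/30 + 1/20) / (1/30 + 1/20)] = √(0.4 × DE + 0.6).

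Example with m = 6 and ICC = 0.10: DE = 1 + 5 × 0.10 = 1.50; 0.4 × 1.50 + 0.6 = 1.20; √1.20 = 1.095.

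| ICC | DE, m = 3 | SE ratio, m = 3 | DE, m = 6 | SE ratio, m = 6 |
|---|---|---|---|---|
| 0.01 | 1.02 | 1.004 | 1.05 | 1.010 |
| 0.05 | 1.10 | 1.020 | 1.25 | 1.049 |
| 0.10 | 1.20 | 1.039 | 1.50 | 1.095 |
| 0.20 | 1.40 | 1.077 | 2.00 | 1.183 |

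**Step 3: check by simulation.** ANCOVA with one baseline covariate (assumed correlation 0.5 with outcome) was simulated 8,000 times per setting. The spread of the estimates divided by the mean reported SE, at ICC 0.05, 0.10 and 0.20, was 1.036, 1.057 and 1.082 for m = 3, and 1.045, 1.113 and 1.207 for m = 6. With ICC 0 it was 1.011 and 1.002. The formula is adequate.

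**Step 4: bearing on the later trial.** With 1:1 allocation and unclustered controls, the size per arm is multiplied by (1 + DE)/2. For illustration, assume a standardised effect of 0.5, 80% power and two-sided 5%: n per arm = (1 + DE) × [(1.960 + 0.842)/0.5]². Without clustering this gives 63. With m = 3 and ICC 0.01 it gives 64; with m = 6 and ICC 0.20 it gives 95.

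**Step 5: what this pilot could say about the ICC.** In the simulations with a true ICC of 0.05, the central 95% of estimates ran from about −0.16 to 0.36 (5 workshops of 6) and from about −0.30 to 0.43 (10 workshops of 3). The chance of a zero or negative ANOVA estimate is P[F < (1 − ICC)/DE], with k − 1 and k(m − 1) degrees of freedom for k workshops. That is 43% (m = 3) to 44% (m = 6) at ICC 0.05, and 33% to 34% at ICC 0.10.

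**The case against.** **The article is brief, and a fuller plan may handle workshops.** Random effects and degrees-of-freedom methods are details that an article usually leaves out. This stands in part: an unseen plan may refine the model. But the article does name a method, and in its usual form that method does not match the delivery it describes.

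**The size is unknown.** This stands. No ICC is given, and at 0.01 the effect is negligible. Groups of 6 are the permitted maximum. Shared exposure may also be incomplete: missed sessions are replaced by individual calls, and about 60% are expected to receive the intervention as defined. If, purely for illustration, only 60% of each workshop shared exposure (effective sizes 1.8 to 3.6), the SE ratios would be 1.01 to 1.03 at ICC 0.05 and 1.02 to 1.05 at 0.10. Expected mean attendance is nevertheless 3 of 4 sessions, so shared exposure is far from absent.

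**A reader might infer inflated false-positive rates or a biased effect.** The documents do not support either reading. The article says that no hypotheses are tested and sets no alpha, the clinical outcomes are secondary, and the point estimate is not materially affected. The feasibility and acceptability outcomes are not tied to this ANCOVA.

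**A reader might infer that the later trial cannot be sized unless this pilot supplies the ICC, or that it will be underpowered.** Neither follows. Nothing says that trial will be sized as if mothers were independent, and an ICC can come from elsewhere. The article mentions a randomised trial of the face-to-face version, which is one possible source. Step 5 shows that this pilot's ICC would be too imprecise to use alone.

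**Conclusion.** The point holds in a limited, conditional form. The named analysis assumes independence in a partially nested design. If the workshop ICC is positive, the true standard error of the arm difference exceeds the reported one by about 0.4% to 1% at ICC 0.01, 2% to 5% at 0.05, 4% to 10% at 0.10 and 8% to 18% at 0.20, for workshops of 3 to 6. These figures rest on an assumed ICC range, equal workshop sizes, equal variances and the full 30/20 split.

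The practical result is an effect size that looks somewhat more precise than it is when carried into planning, and no information on workshop clustering from the stated analysis. No trial conclusion is at risk. It is a worthwhile, inexpensive improvement to a secondary analysis.

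**What to change.** 1. Record a workshop identifier for every intervention mother, prospectively.
2. Analyse each clinical outcome with a partially nested mixed model: t1 score on arm and baseline score, a random workshop effect in the intervention arm only (each control as her own cluster), and Satterthwaite degrees of freedom. The MIXED procedure in the named software, SPSS 27, can fit it.
3. Keep plain ANCOVA as a sensitivity analysis.
4. Report the workshop ICC for the maternal sensitivity scale (ESA) with its confidence interval, as a descriptive parameter under secondary aim 2.
5. Size the later trial over a range of external or assumed ICC values, not from this pilot's estimate alone.

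**Cost.** Some wording and one variable, with no added participants, visits or measurements. The drawbacks are slightly wider intervals, a very imprecise ICC, and a variance component that may be estimated at zero, in which case the model essentially returns the ANCOVA result.
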